## Abstract

**Background:**

In the Netherlands, children start to drink at an early age; of the Dutch 12-year olds, 40% reports lifetime alcohol use, while 9.7% reports last-month drinking. Starting to drink at an early age puts youth at risk of developing several alcohol-related problems later in life. Recently, a home-based prevention program called "In control: No alcohol!" was developed to delay the age of alcohol onset in children. The main aim of this project is to conduct a Randomized Controlled Trial (RCT) to evaluate the effectiveness of the program.

**Methods/Design:**

The prevention program will be tested with an RCT among mothers and their 6 grade primary school children (11-12 years old), randomly assigned to the prevention or control condition. The program consists of five printed magazines and an activity book designed to improve parental alcohol-specific socialization. Parent-child dyads in the control group receive a factsheet information brochure, which is the standard alcohol brochure of the Trimbos Institute (the Netherlands Institute for Mental Health and Addiction).

Outcome measures are initiation of alcohol use (have been drinking at least one glass of alcohol), alcohol-specific parenting, susceptibility to drinking alcohol, alcohol expectancies, self-efficacy, and frequency and intensity of child alcohol use. Questionnaires will be administered online on secured Internet webpages, with personal login codes for both mothers and children. Mothers and children in both the experimental and control condition will be surveyed at baseline and after 6, 12, and 18 months (follow-ups).

**Discussion:**

The present study protocol presents the design of an RCT evaluating the effectiveness of the home-based "In control: No alcohol!" program for 6 grade primary school children (11-12 years old). It is hypothesized that children in the prevention condition will be less likely to have their first glass of alcohol, compared to the control condition. When the prevention appears to be effective, it can easily and relatively quickly be implemented as a standard alcohol prevention program on a large scale.

**Trial registration:**

Nederlands Trial Register NTR2564

## Background

Adolescence is characterized by a strong increase in alcohol use: In 2009, approximately 40% of all Dutch 12-year olds reported lifetime alcohol use, which increases to 70% among 14-year olds and 85% among 16-year olds [1]. Of the Dutch 12-year olds, 9.7% even reported to have been drinking in the last month [1]. Starting to drink at an early age puts youth at serious risk of developing many alcohol-related problems, such as heavy episodic drinking, alcoholism, and cognitive impairments (e.g., [2,3]). These consequences of early onset of alcohol use stress the need to postpone the age of onset. Most school-based alcohol prevention in the Netherlands is conducted at the secondary educational level among 12-15-year olds, while at this age many children have already started to experiment with alcohol. Since many Dutch youth start to drink in early adolescence, prevention programs targeting elementary schoolchildren are needed. However, theory-driven alcohol prevention programs for elementary schoolchildren are lacking.

Socialization theory [4] posits that parents are the main socializing agents in their children's development, especially when it comes to health issues, which has been supported by a wide range of studies [5,6]. Recent studies in the Netherlands showed that through e.g., setting strict rules about alcohol, communicating constructively about alcohol issues, and monitoring daily activities, parents can delay the onset of alcohol use [7-10]. Another reason why parents are important in preventing adolescent alcohol use is that elementary schoolchildren live at home and are still very susceptible to their parents' influences, while peers become more important during mid-adolescence and in some domains parental influence declines [9,11]. Moreover, most children get their first glass of alcohol from their parents [12]. By making parents aware of their role in introducing alcohol to their child, the age of alcohol onset can be delayed (e.g., [8]).

Parental drinking affects adolescent alcohol use through norm-setting and modeling [9,13]. Further, drinking parents tend to engage less in alcohol-specific socialization practices [7,14], probably because they do not consider themselves being credible in prohibiting their children from drinking. However, alcohol-specific socialization strategies like setting rules, monitoring and communicating constructively are also effective when parents are (heavy) drinkers themselves (e.g., [7,15]). Therefore, it is important to empower this specific group of parents to enhance the confidence alcohol-drinking parents have in the effectiveness of their alcohol-specific parenting strategies. The current program addresses this issue by increasing parents' comfort level in communicating with their children about (their own) alcohol use.

Thus, although there is substantial empirical evidence that parents can prevent early onset of drinking by engaging in alcohol-specific parenting, no effective prevention program for parents and primary school children has been implemented in the Netherlands. The prevention program "In control: No alcohol!", which approach is based on a smoking prevention program called "Smoke-free Kids" [16], aims to fill this gap. It is a home-based program, which provides many opportunities to engage in structured interactions for the parents and children. Parents and children can go through the program on their own, when they have time, and are not obliged to engage in a complex, time-consuming program. A pilot study conducted over a period of 6 months has provided some insight into the effective components of the "In control: No alcohol!" program [17]. Specifically, exposure to the program increased the likelihood that mothers make a rule with their children about not drinking before a certain age, that mothers monitor their children, and for mothers that drink alcohol more than average, it increased the quality of alcohol-specific communication.

### Aim and hypotheses

The main aim of this project is to conduct a Randomized Controlled Trial (RCT) to evaluate a recently developed home-based alcohol prevention program, entitled "In control: No alcohol!" The program focuses on alcohol-specific parenting as a tool in delaying the age of alcohol onset in children. Onset of alcohol use is defined as the intake of the first glass of alcohol. With this RCT, including an experimental and a control group, we test whether fewer children have their first drink at an earlier age when included in the program. The second aim is to determine whether the program increases maternal use of several alcohol-specific parenting practices according to mothers and their offspring. The third aim is to test whether the prevention program differs between families varying on parental own drinking.

More specifically, we expect that a) a significant lower percentage of children who followed the program will have had their first glass of alcohol at the last follow-up compared to children who did not follow the program. b) mothers who followed the program are significantly more likely to engage in alcohol-specific parenting than mothers who did not follow the program. We expect that mothers involved in the program (as compared to controls) will set and keep stricter rules about alcohol, are more involved in constructive communication on alcohol-related topics, have more confidence in discussing alcohol matters, reduce children's access to alcohol beverages, make a rule with their children about not drinking before a certain age and are more likely to monitor children's activities. c) Above average drinking mothers that follow the program are more likely to increase their alcohol-specific parenting as compared to below average drinking mothers that follow the program.

## Methods/Design

### Study Design

The prevention program "In control: No alcohol!" will be tested with an RCT with 2 conditions. A total of 656 mothers and their 6 grade children (11-12 years old) will be involved in the experimental group receiving the program, and 656 mothers and their children will participate in the control condition. Mother-child dyads in the control group receive a factsheet brochure on youth alcohol use and the detrimental consequences of alcohol use among children, which is the standard alcohol brochure of the Trimbos Institute (the Netherlands Institute for Mental Health and Addiction). The experimental group receives 5 modules on a monthly basis. After baseline assessment of children and mothers, follow-up assessments will be conducted after 6, 12, and 18 months (see Figure 1). Assessments will be conducted among both children and mothers at each time point.

**Figure 1 F1:**
[figure not shown]
**Study Design**.

At the end of the project, 10 travel checks of 500 euro's will be raffled between families who filled in the questionnaire at each time point. Children will receive a small gift to thank them for participating in the study.

### Participants

#### Recruitment

Respondents will be recruited through a selected sample of primary schools in the Netherlands. Principals of participating primary schools are asked to hand out envelopes for the mothers to children from grade 6 of Dutch elementary school, who are 11-12 years old at the time the prevention starts. This envelop includes a letter in which we ask mothers to participate with their children in a study testing an alcohol prevention program, an informed consent form for themselves and their children, and a response envelop. If mothers and their children want to participate, they can return their contact information by means of the informed consent form in the enclosed response envelop. Also, mothers and children can read information about the study and register online via a webpage.

#### Inclusion criteria

To be included in the present study, children will have to be in grade 6 of Dutch elementary school, when most children are 11-12 years old. Children can only participate together with their mother or a female guardian, and they both have to be able to speak and read Dutch. The form with which mothers and children sign up for the study also serves as an informed consent form. The proposed study and prevention protocols have been approved by the ethical committee of the Faculty of Social Sciences at the Radboud University Nijmegen (ECG16092010).

We focus on grade 6 children (11-12 years old) at baseline, because children start to get increasingly interested in alcohol issues at this age [18], but have generally not drunk their first glass of alcohol yet [19], which makes them an important target group for primary prevention. Providing an alcohol prevention program just before the age of onset, might have a large impact on the health of these children [8]. Inclusion of younger children might not be appropriate, because they will be less likely to consider drinking alcohol themselves. Thus, the period will be too long before they think of trying alcohol. Further, this age group consists of children who are in late childhood, prior to early adolescence. Early adolescence is characterized by increased conflicts with parents, especially with mothers [20] leading to less conformity and openness. This pleads for a focus on the developmental period prior to early adolescence - late childhood - when children are expected to be still quite susceptible to the influence of their parents [21]. While Dutch prevalence figures indicate that 13 to 17% of the 11 years old children drank at least one glass of alcohol [19,22] and we expect this also to be the case in our sample at baseline, we expect that the prevention program "In control: No alcohol!" will significantly lower the increase of this percentage a year later.

We have a few reasons to focus on mothers as target parents: (a) most children spend more time with their mother than with their father, giving mothers the practical advantage of having more time to deliver the alcohol-specific socialization program to their children [23], (b) if parents are divorced, in most cases children live with their mothers [23], (c) women generally are more likely than men to enroll in health-related programs [24], (d) the smoking-specific program also included only mothers, and (e) given the plausibility that program effects would differ by parent gender, including fathers would substantially increase the size and costs of the proposed trial. However, since fathers drink more alcohol than mothers [23], we measure paternal drinking behaviors in the questionnaires of both mothers and children, to be able to control for paternal drinking in the analyses.

#### Randomization

Randomization will take place at the school level, to avoid contamination between conditions. This means that all children in one school will be allocated to the same condition, prevention or control. An independent statistician will perform the allocation of schools to the two conditions.

### Sample Size Calculation

Based on the outcomes of parent-adolescent interventions in the Netherlands and the United States [14,21], we expect a minimal 10% difference in initiation rates between the control and experimental group at the third follow up, which is approximately 12 months after the end of the prevention. Equal cell sizes are assumed for study cells and power of .80 has been targeted. The primary hypothesis, a significant lower percentage of children who have their first glass of alcohol in the prevention group than in the control group, will be tested at an overall significance level of 0.05 (two-sided). G-Power was used to calculate the estimated sample sizes for two-sample comparison of proportions. Based on the prevalence of alcohol use in 13 year olds (age of the children at 18 months follow-up), which is 55%, we need 404 children per condition. However, if we take into account possible attrition (0.80), the fact that data are clustered (mother-child dyads are nested within schools) and the fact that we apply multiple imputation in the case of missing data (factor 1.4), we end up with 656 children per condition ((183/0.80) * 1.4)). Thus, 1312 mothers (and children) are required to participate. In accordance with the intention-to-treat philosophy, all children randomized to one of the conditions are included in analyses to test the study hypotheses.

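### The sample-size calculation does not yield 656 per condition from either printed base, and with the plan's own factors 656 falls short of the targeted 0.80 power

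*Protocol article*

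**What the plan says.** The Sample Size Calculation section of the protocol article gives these design inputs:

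- Effect: "we expect a minimal 10% difference in initiation rates between the control and experimental group at the third follow up".
- Test level: the primary hypothesis "will be tested at an overall significance level of 0.05 (two-sided").
- Power: "power of .80 has been targeted".
- Allocation: "Equal cell sizes are assumed for study cells".
- Reference rate and base number: the prevalence of alcohol use at age 13, "which is 55%, we need 404 children per condition".

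The section then allows for attrition (0.80) and applies a factor of 1.4 for clustering within schools and multiple imputation. It concludes: "we end up with 656 children per condition ((183/0.80) * 1.4"). The total is given as 1312.

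The Study Design section uses the same figure as the enrolment target: "A total of 656 mothers and their 6 grade children (11-12 years old) will be involved in the experimental group", with 656 also in the control condition.

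**The concern.** Two different base numbers appear within two sentences. The text says 404 and the formula uses 183. The 183 occurs nowhere else in the article and is not explained. Neither base reaches 656 with the printed factors, so the defect is more than one mistyped number that the reader can mentally replace.

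The stakes are the enrolment target and the power claim for the primary outcome. The 656 per condition and 1312 in total rest on this calculation alone. If the attrition and 1.4 factors are taken as printed, the target supplies fewer effective children than the plan says it needs.

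**Working it through.** **Inputs** (all from Sample Size Calculation): two-sided 0.05; power 0.80; 1:1 allocation; 55% reference rate, read as the control rate; 10-point difference, hence 55% versus 45%; retention 0.80 as a divisor; 1.4 as a multiplier.

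**Step 1: reproduce the base of 404.** The article names G-Power and a two-sample comparison of proportions, but no specific test. The candidates for 55% versus 45% are:

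| Method | n per condition for power 0.80 |
|---|---|
| Unpooled z-test | 389 |
| Arcsine | about 391 |
| Pooled z-test, uncorrected | 392 |
| Pooled z-test, continuity-corrected | 412 |
| Fisher's exact test | 404 (power 0.7984 at 403, 0.8001 at 404) |

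For example, the pooled z-test uses n = [1.960·√(2·0.5·0.5) + 0.8416·√(0.55·0.45 + 0.45·0.55)]² / 0.10² = (1.386 + 0.592)² / 0.01 ≈ 391.3, rounded up to 392. Fisher's exact test matches the stated 404, so the base is correct.

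**Step 2: apply the inflation as printed** (base / 0.80 × 1.4).

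- Base in the formula: 183 / 0.80 × 1.4 = 320.25, less than half of 656.
- Base in the text: 404 / 0.80 × 1.4 = 707, or 1414 in total.
- Stated: 656, or 1312 in total. This is 707 − 656 = 51 fewer per condition and 102 fewer in total, a gap of 51/707 = 7.2%.

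**Step 3: work back from 656.** 656 × 0.80 / 1.4 = 374.9. The printed factors reach 656 only from a base of about 375, which the article never states.

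**Step 4: power at the effective size.** With about 375 effective children per condition and 55% versus 45%:

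- Fisher's exact test: 0.769.
- Uncorrected pooled z-test: Φ[(0.10 − 1.960·√(0.5/375)) / √(0.495/375)] = Φ(0.0284/0.0363) = Φ(0.783) = 0.783.
- Continuity-corrected z-test: 0.761.

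All three are below 0.80.

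**Step 5: other ways to reach 656.**

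- 404 / 0.80 × 1.3 = 656.5. This fits, but it needs a factor of 1.3 that is not in the text.
- 404 × 1.2 × 1.4 = 678.7. This does not fit.
- 392 × 1.2 × 1.4 = 658.6. This is close, but it uses neither the stated 404 nor the printed division by 0.80.
- 65% versus 55% by pooled z-test: n = 376, and 376 / 0.80 × 1.4 = 658. This is close, but it abandons 404.

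**The case against.** No one can defend the printed formula. The strongest reply concerns the power shortfall. It depends on 1.4 being right and 656 being wrong. If the factor actually used was 1.3, 656 follows from 404 to within rounding and nothing is lost. A formula already corrupt in one entry is weak evidence for its other entries. This stands as a possibility, but 1.4 is printed twice, in the sentence and in the formula, and 1.3 nowhere. Even if 1.3 was used, the text would then misstate its only allowance for clustering and imputation and would still need correction.

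A second reply is that the shortfall is small and depends on the method. That is true. It is about three points by Fisher's test and under two by the uncorrected z-test. Against the z-test requirement of 392, an effective 375 is about 4% short rather than 7%. The planned primary analysis is a logistic regression that accounts for clustering, so 0.77 and 0.78 describe the sizing calculation and not the final model.

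A third reply reads 55% as the lower rate. Power at 375 for 65% versus 55% is then 0.799 by z-test. That reading does not produce 404, however, and it sits badly with a program expected to lower initiation below the population rate.

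Finally, a base of 183 would give power of only about 0.48 for 55% versus 45%. That is not the trial's actual position, because 656 per condition is stated consistently as the number to be enrolled.

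**Conclusion.** The point holds. As printed, 656 follows from neither 183 (which gives 320) nor 404 (which gives 707), and no other base is stated. The base of 404 is right, so the fault is in carrying it forward to the enrolment target.

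With the plan's own factors, the target is 51 children per condition (102 in total) below what 404 requires. Power is about 0.77 by Fisher's exact test or 0.78 by the uncorrected z-test, against 0.80. This rests on three assumptions: 55% is the control rate, the retention of 0.80 is correct, and 1.4 is the intended factor. The failure of the arithmetic needs none of these assumptions. The power loss is modest; the main defect is that the stated sample size has no valid derivation.

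**What to change.** Delete 183 and print one calculation in which base, factors and total agree. Two versions are consistent with the printed factors:

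1. Keep 656 per condition and 1312 in total. State that this corresponds to about 375 effective children per condition, with power of about 0.77 (Fisher's exact test) or 0.78 (uncorrected z-test) for 55% versus 45%. Name the test used.
2. Keep power 0.80 and print 404 / 0.80 × 1.4 = 707 per condition, 1414 in total. Change the Study Design section to match.

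If the sponsor's records show that a factor other than 1.4 was applied, print that factor and what it covers, and restate the power only if the reconciled inputs require it.

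The first version changes wording only: no added participants, no design change, and a slightly less favourable power statement. The second adds 102 mother-child dyads to the target.

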### Program

#### Theoretical basis of the program

The program was structured around two theories to meet the prevention objectives: Social Cognitive Theory and models of persuasive communication for attitude and behavior change. Fundamentals of child socialization were derived from Bandura's Social Cognitive Theory [4] and consisted of perception (the articulated thoughts and actions of parents or other socializing agents are noticed by the child); cognitive rehearsal (recall and assignment of meaning to what has been noticed by the child); behavioral rehearsal (rehearsal of the things learned while receiving feedback regarding these thoughts and behaviors); and motivation (reinforcement for certain communications and actions). Every part of the program addresses one or more of these child socialization processes.

The Elaboration Likelihood Model [25] contributed to the design of persuasive communication. This model states that participants can differ in the degree to which they experience the program being relevant or obvious. While designing the prevention content and layout, this should be taken into account. For example, some parents will respond to program recommendations most through message content while others' may be most affected by peripheral cues such as print design. Both content and layout are taken into account while structuring program information.

Other program design strategies which are theory-based and have been used to develop the alcohol-specific socialization program include: (a) allow participating parents to exercise choice regarding when and how to implement program objectives, which will increase the probability that for example alcohol using parents will participate, (b) begin with "small wins" that are easy to achieve and build parental confidence, and thereafter, promote gradual change in socialization activities, (c) dedicate part of the prevention to developing the requisite skills, such as parent-child communication skills, needed to implement other program recommendations, (e) build program recommendations on alcohol-specific socialization literature, and (d) use multiple reinforcers, including self-monitoring and feedback (and a small financial incentive at the end) to maintain involvement and motivation.

#### Prevention condition

The proposed program, "In control: No alcohol!", consists of 5 modules which families receive by mail every 4 weeks for a period of 5 months. A module consists of an attractive magazine including information, games, quizzes, and puzzles for parents and children to complete together. These structured interactions for the parent and child is a key technique for facilitating parent-child engagement in the program. The magazines' content is based on the empirical evidence of alcohol-specific parenting in the delay of early alcohol intake (e.g., [7-9,26]).

Each of the five magazines addresses different important issues regarding youth alcohol use and child socialization. Magazine 1 consists of general information about alcohol, alcohol use among children and the importance of parenting behavior, such as anti-alcohol norms and parental supervision. Magazine 2 addresses the risks of alcohol use, especially among children, and parental attitudes towards early drinking. Magazine 3 focuses on parental modeling of alcohol use and the effectiveness of setting rules about alcohol, also for parents who use alcohol themselves. Magazine 4 aims at enhancing awareness about peer influence and increasing the ability to handle peer pressure, while magazine 5 discusses the influence of alcohol-related media and again stressed the eminence of setting clear and strict rules. In addition to these specific topics, each magazine contains general information and practical tips on high-quality parent-child communication in order to gradually increase parents' skill and comfort level in communicating with their children about alcohol.

In addition, with the first magazine the child receives a personalized activity book ("Logboek"). The activity book provides the child the opportunity to repeat what he/she learned about alcohol in a playful and personal way. It is also an extra stimulus to be active in the program. With the activity book, each child receives a personal login code for the related secured website http://www.houvolgeenalcohol.nl. The login code provides access to more games, puzzles and pictures related to the prevention program. The child can download the completed website activities and put them in his/her activity book, so he/she can create his/her own glossy journal.

